#### Cognitive tests

The cognitive test battery includes visuo-spatial working memory and a 1-back working memory task.

##### Visuo-Spatial Working Memory Task

Visuo-Spatial Working Memory (VSWM) task is a self-ordered search task, which assesses an individual’s ability to store and manipulate information about the location of objects on a computer screen [50]. First, the test displays three filled circles on a computer screen (level 3). The participant must find a red dot behind one of the circles by touching each of the circles one at the time. The objective is to touch as few times as possible at each level. The red dot can only be positioned behind one circle and must be dragged to a column on the right side of the screen, when found. The red dot cannot be placed behind the circle more than one time at a given level. When a given level is finished, the participant continues to the next level where there are additional number of circles. The number of circles increases until there are ten circles on the screen. The placement of the circles is randomly distributed from trial to trial. The test measures time to complete each level, the number of errors made and the number of times the participant changes search strategy during the trials. Errors are defined as touching circles where the red dot cannot be (i.e., either previously found or already touched). The outcome measure will be a score based on time, error and strategy during the last three levels.

##### 1-back working memory task

Updating of working memory is assessed using a 1-back task. This 1-back task is constructed of representations of symbols (e.g., car, cloud, key, eye and bicycle); one symbol is presented at the time. The child must compare the symbol seen on the screen with the symbol previously presented. Children are instructed to press “yes” (a green key) on the keyboard if these two symbols are identical and “no” (a red key) if they are dissimilar, as fast, and as accurate as possible. The test consists of 20 practice trials followed by one test block of 20 trials (both 30% “yes” trials). Symbols are presented for 500 ms followed by a 3000 ms blank screen. The response window and inter-stimuli interval is 3500 ms each. The results from the test constitute number of correct and wrong “yes” and “no” answers, mean reaction time for correct “yes” and “no” answers, and number of non-responses in the test block. Normative data on the n-back task for children and young adolescents have previously been reported [51].

#### Physical Tests

##### Andersen Test

Cardiorespiratory fitness will be measured using the Andersen-test, a 10-minute intermittent running test (15 s running and 15 s pausing), running back and forth on a 20 m track [52]. Total distance covered will be used to represent cardiorespiratory fitness. Verbal encouragement is given to encourage maximal performance. If an obvious submaximal performance by a child is seen, the results will be discarded. This test has been proven valid and reliable compared to direct measures of maximum oxygen uptake in a similar cohort [53]. The Andersen-test has demonstrated reliability and validity for the target age group [54].

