### Randomized controlled trial (RCT)

The overall aim of the ACTIVE SCHOOL RCT study is to investigate the effects of two different types of in-school PA interventions on academic performance in children aged 9–10 years (3rd grade). The cluster RCT has three arms and includes two intervention groups; (1) RJF and (2) ML, and (3) control group (CG). The interventions are planned for one school year carried out in two rounds during the school years 2023/2024 and 2024/2025. The randomization will be stratified at the school level with an approximate 1:1:1 recruitment protocol (RJF:ML:CG). Approximately nine schools will be allocated to each arm (see *Randomization*). Due to the study design, blinding of instructors, teachers and participants will not be possible, which is common practice in school-based studies.

Schools from all regions of Denmark will be recruited by phone, e-mail, relevant websites, and digital/social media targeting school staff and school principals. If principals and school staff agree to participate in the study, an informal project meeting will be held, and comprehensive information will be provided.

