#### Outcome measures

To evaluate the effects of the interventions, children will be assessed before (T0) and after the intervention period (T1). Assessments will be carried out by research staff trained by senior research team members of ACTIVE SCHOOL and will be performed during school hours. Outcomes measured to assess potential effects of the two interventions (RJF and ML) include academic performance in math (primary outcome) and Danish, cognitive functions (working memory tasks), motivation for school, well-being, anthropometry, cardiorespiratory fitness, and physical activity level as secondary outcomes. Data entry will be performed onsite in REDCap using laptop computers and written on paper for random sample quality testing. REDCap is a secure web application for building and managing online surveys and databases [42]. Additionally, objective PA measures will be conducted at T0, T1 and at some schools also during the intervention. Implementation outcomes will be assessed on a regular basis (see below).

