#### Motivation

Children’s motivation for school will be assessed with the Self-Regulation Questionnaire-Academic (SRQ-A) [57]. SRQ-A is a domain specific, self-reported questionnaire developed and validated for children in primary and lower secondary school [37]. The SRQ-A originally measures four types of motivation (or behavior regulation) for engaging in schoolwork and learning activities identified in the Self Determination Theory; intrinsic motivation, identified regulation, introjected regulation and external regulation. However, in this study only the two autonomous types of motivation; intrinsic motivation and identified regulation, will be measured to shorten the questionnaire to10 questions. The questionnaire will be administrated electronically in REDCap. A trained person will aid the children with reading each item while they complete the questionnaire on a computer.

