#### Organizational structure and responsibilities

The research team behind the ACTIVE SCHOOL project is a multidisciplinary group of experts in PA, school context, cognition, learning, motivation and childhood health. This team is responsible and handles all aspects of the study management including recruitment, training of intervention deliverers and test personnel, data collection and handling, final analysis and reporting of results. Since the ACTIVE SCHOOL project was initiated, an international multidisciplinary advisory board has been assigned. The board has ensured scientific quality in all aspects of the project.

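### The reason given for not blinding instructors, teachers and pupils does not reach the research-staff testers or the analysts, and nothing in the protocol masks them

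*Protocol article*

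**What the plan says.** The section Randomized controlled trial (RCT) deals with blinding in one sentence: "Due to the study design, blinding of instructors, teachers and participants will not be possible, which is common practice in school-based studies". It names three groups. Testers and analysts are not among them.

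The Outcome measures section gives most of the testing to a different group: "Assessments will be carried out by research staff trained by senior research team members of ACTIVE SCHOOL". The academic tests are the exception, since the section on academic performance tests assigns them to the schools' own teachers.

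Two research-staff outcomes involve direct interaction with the child. For the Andersen Test, "Verbal encouragement is given to encourage maximal performance". For the motivation questionnaire, "A trained person will aid the children with reading each item while they complete the questionnaire on a computer".

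Under Organizational structure and responsibilities, one research team handles all study management, "including recruitment, training of intervention deliverers and test personnel, data collection and handling, final analysis and reporting of results". The analysis section says the models will adjust for confounders found to be unevenly spread across the arms at baseline. It adds a per-protocol analysis restricted to classes judged compliant from the teachers' text-message survey.

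The only masking described is in the Randomization section: the independent statistician who drew up the list knew neither the content of the interventions nor which schools were which.

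**The concern.** Those who deliver or receive a school activity programme cannot be blinded to it. Someone who arrives to run a fitness test, or who fits the model, could be kept unaware of the arm at least in part. The protocol gives a reason that covers the first group and makes no provision for the second.

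This matters where the measurer can move the result. Distance in a ten-minute intermittent run depends on effort, and effort responds to encouragement. Run, Jump & Fun is a moderate-to-vigorous activity programme, so a tester who knows the arm may expect better fitness there and encourage accordingly. Help with reading questionnaire items leaves similar room for prompting. A bias of this kind runs in the expected direction, and recruiting more schools does not remove it.

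On the analysis side, choosing covariates after looking at baseline imbalance leaves room for judgement. An analyst who knows which arm is which can, without intending to, prefer the choice that gives the expected answer.

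**Working it through.** The protocol states no figure on this point, so the main check is textual. An illustrative calculation follows.

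**Who is masked, by role**

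| Role | What the article says | Does the stated reason for no blinding apply? |
|---|---|---|
| Instructors, teachers, pupils | Cannot be blinded (RCT section) | Yes |
| Statistician who made the list | Unaware of content and school identity (Randomization) | Not needed |
| Research-staff testers | Nothing on masking (Outcome measures) | No |
| Analysts | Nothing on masking (analysis section; Organizational structure) | No |

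**Could testers learn the arm?** Project personnel attend two set-up meetings at each Run, Jump & Fun school and one at each Move & Learn school. Observations are also made in schools (Implementation). Nothing stops the same people from testing there later. The article does not say that they do.

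**Which outcomes are exposed?**
- Andersen distance: exposed, because it depends on effort and encouragement.
- Motivation: exposed, because a trained person aids the reading of each item.
- Well-being: possibly exposed. Items are read aloud, but the reader is not named.
- Waist: little exposed, because repeat measurements are required.
- Working-memory tasks: little exposed, because they run on a computer and are scored on responses, errors and times.
- Accelerometry: little or not exposed, because it is device-recorded.
- Math: outside the tester concern, because teachers run it and the test publisher collects the results.

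**Illustration of size**

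Inputs from Sample size and power: 9 schools per arm, 20 children per school (one class), ICC 0.15. That ICC is given for math; using it for running distance is an assumption. The tester effect d, in SD units, is also assumed, because the article gives none.

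- Variance of a school mean = 0.15 + (1 − 0.15)/20 = 0.15 + 0.0425 = 0.1925.
- SE of the difference between two arms = √(2 × 0.1925/9) = 0.2068 SD.
- Cross-check by the design effect: 1 + 19 × 0.15 = 3.85; effective n per arm = 180/3.85 = 46.75; √(2/46.75) = 0.2068. The two agree.
- With no true effect, the one-sided false-positive rate is 1 − Φ(1.645 − d/0.2068).
- The two-sided rate is 1 − Φ(1.960 − d/0.2068) + Φ(−1.960 − d/0.2068).

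| Assumed d (SD) | d/SE | One-sided 5% | Two-sided 5% |
|---|---|---|---|
| 0 | 0 | 0.050 | 0.050 |
| 0.05 | 0.242 | 0.080 | 0.057 |
| 0.10 | 0.484 | 0.123 | 0.077 |
| 0.20 | 0.967 | 0.249 | 0.162 |

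The table shows what a given tester effect would do. It is not evidence that one exists.

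**The case against.** The strongest reply is that this is silence in a condensed article. Test manuals, staffing rotas and coded arms usually sit in a full protocol or analysis plan, which are not shown. The feasibility section says test procedures were standardised and adjusted before the trial, and nothing says that encouragement varies between arms or between time points. Educators from a university college, not the testers, train the school staff. The paragraph on responsibilities describes a team, and does not say that the same individuals set up schools, test and analyse.

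Much of this stands, and it limits the point. A reader might infer that the plan has given up masking altogether, or that testers do know each school's arm. The text supports neither: it names three unblinded groups, describes one masked person, and is silent on the rest. A reader might also carry the concern over to the primary outcome. That is not supported either, since teachers run the math test, and the article already lists this among its limitations.

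What does not fall away is that the article addresses blinding, gives a reason, and that reason stops short of two roles that matter. It acknowledges possible data-collection bias for the teacher-run test, but says nothing about the staff-run tests, where the risk is easier to reduce.

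It is also fair to say that masking testers inside a school, during school hours and among pupils who know their arm, will be only partial.

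**Conclusion.** The point holds as a cheap improvement to secondary outcomes and to the analysis. As written, the protocol leaves an avoidable route to bias in the Andersen distance and the motivation score, and leaves the covariate choice open to analysts who know the arms. It does not show that such bias occurs.

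The size is unknown. The rates of 8%, 12% and 25% one-sided (6%, 8% and 16% two-sided) rest on assumed tester effects of 0.05, 0.10 and 0.20 SD and on an ICC borrowed from math. They are illustrative only. The rule for discarding submaximal runs is a separate matter and is not relied on here.

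**What to change.** In the RCT section, after the sentence on blinding, add that:

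1. Testers at the end of the intervention (T1) are not told the school's arm. Where existing staffing allows, staff who set up or observed a school do not test there.
2. Encouragement in the Andersen test uses the same words at the same times in all arms, and questionnaire items are read verbatim in all arms.
3. Testers record whether they learned or guessed the arm.
4. Analysts receive arms coded A/B/C, with the code held by the independent statistician, until covariates and analysis sets are locked.

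The cost is a short script, one extra field on the test-day form and a coded variable. The staffing rule could need more testers if applied without exception, hence the qualifier. Schools in the 2024/25 round had not yet been told their arm when the article was written, so that round at least could adopt all of this.

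Two downsides remain. Pupils will sometimes reveal the arm, which the arm-guess field will show. Coding also protects the per-protocol set less well than the covariate choice: fidelity to the principles is surveyed only in the two intervention arms and is specific to each, so those data may reveal the arm.

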##### Accelerometry

PA will be assessed using accelerometer measurements (Axivity, Newcastle, UK) for one week before the intervention starts (T0), once during the intervention at randomly selected schools (but not the full sample), and one week for all schools towards the end of the intervention (T1). Children will wear the accelerometer for seven consecutive days taped on their right thigh. Data for a full day will be analyzed with minimum wear-time requirements of 8 h/day. ACTi 4 software (Version 14.09, ACTi Corp., Copenhagen, Denmark) will be used to identify different types of PA such as sitting, standing, walking, fast walking, running, cycling, sit-to-stand movements, and steps taken. The amount of time spent on each activity type each day will be calculated and time spent in different PA intensity levels according to the recommendations will be reported [55].

#### Wellbeing

Children’s wellbeing and quality of life will be assessed using the Kidsscreen-27 questionnaire. The Kidsscreen-27 is a valid and reliable tool for measuring health-related quality of life and wellbeing in children and adolescents. The questionnaire has been used in various research projects to gain insights into the subjective experiences and perceptions of young people regarding their quality of life and well-being [56]. Kidscreen-27 assesses the following 5 domains of health related to quality of life: physical well-being (5 items), psychological well-being (7 items), relation to parents and autonomy (7 items), social support and peers (4 items), and the school environment (4 items). The original questionnaire consists of 27 items and is structured in a series of questions answered on a five-point Likert scale, ranging from “never” to “always”. As this intervention is school-based only, the parent and the autonomy domain are not included in this study. The questionnaire will be administered in a paper version and every item will be read aloud for the children to overcome any reading difficulties.

#### Motivation

Children’s motivation for school will be assessed with the Self-Regulation Questionnaire-Academic (SRQ-A) [57]. SRQ-A is a domain specific, self-reported questionnaire developed and validated for children in primary and lower secondary school [37]. The SRQ-A originally measures four types of motivation (or behavior regulation) for engaging in schoolwork and learning activities identified in the Self Determination Theory; intrinsic motivation, identified regulation, introjected regulation and external regulation. However, in this study only the two autonomous types of motivation; intrinsic motivation and identified regulation, will be measured to shorten the questionnaire to10 questions. The questionnaire will be administrated electronically in REDCap. A trained person will aid the children with reading each item while they complete the questionnaire on a computer.

#### Implementation process evaluation

To evaluate the implementation of the interventions, the Reach, Effectiveness, Adoption, Implementation, and Maintenance (RE-AIM) framework will be used as a guide [58]. The RE-AIM framework is widely used to plan, guide and evaluate intervention studies and expand the knowledge of “how and why”. Definitions of the RE-AIM implementation outcomes adapted to ACTIVE SHOOL are displayed in Table 2. The outcomes will be assessed both quantitative and qualitatively and will be collected on multiple levels (child, teacher, school management).

**Table 2 Tab2:** Dimension definitions of RE-AIM in ACTIVE SCHOOL process evaluation

Evaluation dimensions definitions of RE-AIM	
**Dimension**	**Definition**
Reach	Refers to recruitment strategy and procedure for this. Refers to the proportion and representativeness of included schools and children.
Effectiveness	Refers to the effect of the interventions on academic performance, cognitive performance, motivation and well-being in intervention group children compared to the control group, who do not receive the intervention.
Adoption	Refers to the principal’s decision to accept the intervention as a part of a school year, and staff decision to adopt the intervention or not. This is reported as the acceptability, appropriateness rated by the staff and their delivery of any part of the intervention.
Implementation	Refers to the staff adherence to the target minutes of the intervention and the fidelity to intervention principles delivered as intended. Feasibility and adaptability additionally refer to implementation quality.
Maintenance	Refers to the extent to which intervention implementation was maintained throughout the school year (short-term maintenance). Additionally, indicators of sustainability are identified.

##### Reach

In the present study, the reach dimension reports how the recruitment of schools is executed, as well as the size and representativeness of the included school. Also, the strategy for recruiting children is reported. Reach also covers demographic description of parents/guardians of the participating children and the teachers, where the proportion of consents returned will be a measure of willingness and commitment to the project.

##### Effectiveness

Effectiveness is to which extend the interventions affect academic, cognitive, physical and motivation outcomes, as described in *Outcome Measures*.

##### Adoption

Adoption is a measure of the acceptability and understanding of the interventions experienced by the school staff assessed both quantitatively and qualitatively.

Teachers and pedagogues will complete the survey Usage Rating Profile-Intervention (URP-I) before the interventions begin, midway and at the end of the intervention period [59]. URP-I is a validated, self-reported questionnaire containing 29 items covering six factors: acceptability, understanding, feasibility, system climate, and system support. Each item is rated on a scale from 1 (Strongly disagree) to 6 (Strongly agree). A summed score will be calculated for each of the factors. The original URP-I is translated into Danish following a protocol of a four-step-process inspired by WHO guidelines [60].

Additionally, adoption will be evaluated by interviews with school staff involved in the study. Teachers, pedagogues, and school principals will be invited to focus group interviews. The purpose of the interviews is to gain deeper understanding of how the interventions were adopted into practice and which adaptations were made. Interviews will be conducted in the last months of the intervention. The interviews will follow a semi-structured guide, be transcribed verbatim and undergo reflexive thematic analysis [61].

##### Implementation

The implementation evaluation will give comprehensive knowledge of how the interventions are implemented in the schools and how they are adapted to the specific schools’ context. Implementation fidelity will be evaluated in a self-reported SMS survey sent out every week throughout the study period. The teachers/pedagogues will receive a SMS with a link to a short survey, which can be answered from their mobile phones. These surveys will be distributed, and data will be collected and stored using REDCap. The survey questions will assess adherence in all three groups (RJF, ML and CG), in terms of the total minutes of PA delivered. In the two intervention groups fidelity will be measured, in terms of how closely the intervention principles were followed over the previous week. The feasibility of the implemented strategies will also be measured with the URP-I questionnaire and within the aforementioned focus group interviews. Furthermore, observations will be conducted in the schools [62].

##### Maintenance

Maintenance will be measured six months after the beginning of an intervention and onwards [63]. Answers on delivery of minutes of PA from SMS survey will be the outcome. Furthermore, group interviews will cover intentions to maintain the interventions after the end of the intervention period.

#### Plan for data management, analysis, and statistics

Descriptive statistics across groups will be summarized and presented. Flow diagram of participants will be described and presented according to the Consolidated Standards of Reporting Trials (CONSORT) 2010 for randomized controlled trials [64]. Differences at baseline between participants included and excluded in the main analyses will be presented (e.g., drop-out analyses) and data will be analyzed for between-group differences (interventions vs. control) at baseline for all outcomes. The effects of the intervention on both primary and secondary outcomes will be tested in intention-to-treat analysis using multilevel mixed models with group (interventions/control) as fixed effect and adjusted for relevant confounders not evenly distributed between groups at baseline. School and class will be included as random effects in the model to account for the cluster structure of the data. Furthermore, per-protocol analysis will be performed including only children from classes compliant with the intervention principles (based on SMS-survey answers from teachers/pedagogues). The statistical analysis will be performed using R (R Core Team, 2022) and in the IMB Statistical Package for the Social Sciences (SPSS) version 24.

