#### Sample size and power

Schools are the units of cluster-randomization. A conservative power estimation with an expected effect size of 0.42 for the main outcome (general math, based on results from [17]) and an intra class correlation of 0.15, resulted in a sample of ≥ 9 schools per intervention arm (27 in total), with a mean of 20 children per class and a minimum of one class per school (power 0.8, 1-tailed, α = 0.05). Mixed-effects models will be used to test the between-group difference (intervention vs. control) for the main outcome (general Math), controlling for baseline values and including school and class as random effects [41].

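### The analysis section picks covariates by observed baseline imbalance and does not carry over the baseline-value adjustment stated elsewhere for math; for secondary outcomes no such adjustment is stated

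*Protocol article*

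**What the plan says.** The protocol article describes the model in two places.

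- **Sample size and power.** For general math only, a mixed-effects model tests intervention against control, "controlling for baseline values and including school and class as random effects". The baseline term carries no condition.
- **Plan for data management, analysis, and statistics.** For primary and secondary outcomes alike, the effect is tested in "multilevel mixed models with group (interventions/control) as fixed effect", with school and class random, and "adjusted for relevant confounders not evenly distributed between groups at baseline". The preceding sentence plans that "data will be analyzed for between-group differences (interventions vs. control) at baseline for all outcomes". This section does not mention the outcome's own baseline value and gives no criterion for uneven distribution.

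The Outcome measures section has children assessed at T0 and T1. The math test is MAT2 at T0 and MAT3 at T1.

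**The concern.** A covariate earns its place by predicting the outcome, not by differing between arms. A rule based on imbalance can leave out a strong predictor because it looks balanced and admit a weaker one because it happens to differ. What counts as uneven is settled only once T0 data are in, and the answer can differ from one outcome to the next.

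The T0 score is usually the strongest predictor available, and with about nine schools per arm its precision is worth having. The general analysis section does not secure it. For secondary outcomes, no section does.

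**Working it through.** **Inputs from Sample size and power:** "with an expected effect size of 0.42 for the main outcome"; "an intra class correlation of 0.15"; "power 0.8, 1-tailed, α = 0.05"; and at least 9 schools per arm, "with a mean of 20 children per class and a minimum of one class per school".

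**Assumed, because the article gives neither:** the baseline-outcome correlation r (0.5 to 0.8, taken as equal at school and child level) and the cut-off for imbalance (p<0.05, then p<0.5).

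**Step 1: the plan's own figure, without baseline.**
- Children per arm: 2 × (1.645 + 0.842)² / 0.42² = 70.1.
- Design effect: 1 + 19 × 0.15 = 3.85.
- Schools per arm: 70.1 × 3.85 / 20 = 13.5, against the stated 9.
- Variance of a school mean: 0.15 + 0.85/20 = 0.1925. SE of the difference with 9 v 9: √(2 × 0.1925 / 9) = 0.207.
- Power: Φ(0.42/0.207 − 1.645) = 0.65, or 0.62 with a t reference on 16 df.

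The stated 9 per arm is therefore not reproduced without a baseline gain. That is a separate matter, but it shows why the baseline term matters here.

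**Step 2: baseline always included.** The SE is multiplied by √(1 − r²). At r = 0.7 it is 0.207 × 0.714 = 0.148, and power is Φ(0.42/0.148 − 1.645), about 0.88 to 0.89. The same formula gives 0.76, 0.81 and 0.96 at r = 0.5, 0.6 and 0.8. Power of 0.80 with 9 per arm needs r of about 0.58 (normal) or 0.63 (t).

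**Step 3: the imbalance rule.** School means were simulated for 9 v 9 schools, 50,000 trials per setting. Each trial was analysed three ways with t references, which is why these powers lie below step 2.

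| r | Baseline never in | Always in | In only if imbalanced, p<0.05 | Null rejection under the rule |
|---|---|---|---|---|
| 0.5 | 0.62 | 0.70 | 0.62 | 0.047 |
| 0.6 | 0.62 | 0.76 | 0.62 | 0.043 |
| 0.7 | 0.62 | 0.84 | 0.63 | 0.040 |
| 0.8 | 0.62 | 0.93 | 0.63 | 0.038 |

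Repeat runs agree to within about 0.01: power under the rule is 0.62 to 0.64, and null rejection 0.037 to 0.047. Under randomisation the p<0.05 test selects the baseline score in only about 5% of trials, so the other 95% use the unadjusted model. The unadjusted standard error gives no credit for the balance observed, so the test is conservative.

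**Step 4: a looser cut-off.** With p<0.5 at r = 0.7, power is about 0.73. That is a smaller loss than 0.63 against 0.84, but still a loss.

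**Step 5: the two sections read together for math.** Baseline is always in, and one further covariate (assumed correlation 0.3 with the outcome residual) enters only if imbalanced at p<0.05. Power is 0.828 against 0.832 without that covariate at r = 0.7, and 0.753 against 0.756 at r = 0.6. Type I error is 0.049 and 0.047.

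**Secondary outcomes.** The article gives no effect size, ICC or correlation for them, so no loss is calculated.

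**The case against.** The strongest reply is that the baseline score has not been removed. The sample-size section states it for math without condition. The analysis section repeats the same random effects and neither excludes the T0 score nor makes it depend on imbalance. A condensed article need not state a term twice. This stands: it is an omission, and on the joint reading the primary analysis loses almost nothing (step 5).

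Three further points stand in part.
- The p<0.05 cut-off and r are assumptions, and the article does not say outright that the baseline comparisons select the covariates. The size of the loss therefore depends on inputs from outside the document.
- The word relevant in the rule narrows the candidates, though it does not say how.
- Not every imbalance need be chance. Schools learn their arm before the summer holiday, and consent is required only before baseline measurement, so the article does not exclude consent given after allocation is known. That still does not make imbalance a sound selector.

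It may also be said that a covariate list belongs in an SAP that is not shown. A missing list is indeed no finding. A stated selection rule is different: an SAP that follows it inherits the weakness, and one that does not departs from the published protocol.

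**Conclusion.** Two things hold on any reading: the article states a covariate rule based on observed imbalance, and it states no baseline adjustment for secondary outcomes. For math, the analysis section should carry over the baseline term given in the sample-size section.

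The size is conditional. If the analysis section alone governed math, power would be about 0.62 to 0.64 instead of 0.70 to 0.93 over r = 0.5 to 0.8, with a p<0.05 selector and the plan's own effect size, ICC and 9 v 9 schools.

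A reader might infer more than this.
- **That the plan abandons baseline adjustment for its primary outcome, so that this power loss is certain.** The sample-size section says otherwise for math.
- **That this selection mechanism inflates the false-positive rate.** In the simulation it makes the test slightly conservative.
- **That it decides whether the trial is informative.** Even with baseline always included, power is only 0.70 at r = 0.5, and the school count is a separate question.

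This is a free improvement to the wording.

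**What to change.** In the analysis section:
- State that the model for every outcome measured at T0 always includes the child's own T0 value of that outcome (MAT2 when the outcome is MAT3).
- Replace the imbalance rule with covariates fixed in advance on prognostic grounds, in the protocol or the SAP. Terms such as intervention round, sex or age are options and are not needed to cure this defect.
- Present baseline comparisons descriptively and do not use them to choose the model.

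In the sample-size section, refer to this same model.

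The cost is wording only. The T0 measurements are already planned, and no school, visit or test is added.
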